### Data Collection, Management, and Analysis

Three types of data are collected for this study, including survey data (participant and community), secondary data (on violence and community context), and implementation data (including observations, participation tracking, interviews, memos, and feedback surveys). As described below, these data are collected to capture outcomes at 2 levels of analysis and across multiple time points, as well as implementation across sites and time.

### Data Collection and Sourcing

For the purpose of measuring the individual-level outcomes (collective efficacy and exposure to violence) and covariates, survey data are collected across the following 3 time points: baseline (T1), the end of the phase II intervention training sessions, and comparison health sessions (T2), and follow-up approximately 8 to 12 months after baseline and to coincide with the completion of the community project for the intervention group (T3). The surveys are anonymous and linked by a personal study code that participants create by answering a series of questions that only they know the answer to at the beginning of each survey. This method of using a personal study code was selected to ensure anonymity and increase the likelihood of honest responses [40], especially for questions related to the use of violence. Baseline surveys are completed in person using paper surveys or tablets, depending on preference; T2 and T3 surveys are also completed in person on paper or a tablet or remotely using survey links that are texted or emailed to participants.

Secondary outcomes (neighborhood collective efficacy and incidence of violence) are measured at the neighborhood level. Neighborhood collective efficacy is captured through a community survey conducted at 2 points in time (T1 and T3). Incidence of violence is sourced from violent crime data for City of Pittsburgh neighborhoods obtained from the Pittsburgh Bureau of Police open data portal, while data for municipalities outside the city (eg, Wilkinsburg, Duquesne, Turtle Creek, and Braddock) are drawn from the Pennsylvania Uniform Crime Reporting system and Allegheny County sources, including police blotter data and the county’s integrated data warehouse. Incidents are geocoded, counted within neighborhood US Census tracts, and normalized by the population size for those tracts.

In addition to data collected for outcome analyses, data are collected to understand how the CRCEI is implemented, how implementation varies across neighborhoods, and factors affecting implementation, focusing on dimensions of fidelity, responsiveness (including engagement, satisfaction, and impact), reach, dosage, characteristics, and adaptation. Data sources include (1) feedback questionnaires completed by participants after the end of each CRCEI (note: participants in the health topics sessions also provide feedback, and those data are not part of the implementation science study); (2) semistructured observation forms completed by RAs during each CRCEI training session; (3) interviews with CRCEI team members (after every 3 neighborhoods) and community partners and facilitators (after phase II in each neighborhood) conducted by a project manager or coinvestigator; (4) confidential, semistructured interviews with CRCEI participants (between phase II and T3 data collection) conducted by a project manager or coinvestigator; (5) unstructured field notes from CRCEI team meetings collected by a coinvestigator; (6) attendance records documented by RAs during all training sessions; and (7) secondary data sources on community contexts (eg, US Census data and community violence data). Interviews with CRCEI team members, participants, and community partners and facilitators focus on experiences with the program and are used to guide ongoing implementation, including sustainability in the participating neighborhoods. Interviews with CRCEI team members also provide insight into adaptations, characteristics, and barriers to and facilitators of implementation. Qualitative data are complemented with quantitative data from the feedback questionnaires. Attendance records during each session speak to reach, dosage, and responsiveness (engagement). Finally, secondary data are sourced from the US Census and local police data to understand contextual features of each neighborhood.

### Data Management

Participant surveys and community surveys are primarily web-based (backup paper surveys are used as needed) on tablets using REDCap (Research Electronic Data Capture) hosted at the University of Pittsburgh, an online data management and survey system [41]. Responses to the anonymous web-based secure survey are entered by the participants themselves on an electronic tablet; no data are stored on the computers themselves. Only research staff who have been added to the project can access this online database. Data are downloaded and stored on a password-protected shared drive that can only be accessed by users with the appropriate permissions. No names are connected to the survey data, as each participant creates their own secret code as described earlier.

The only study documents that contain unique personal identifiers are contact forms and the contact list of participants to assist with recontacting participants for follow-up surveys. Contact forms are stored in a secure file drawer inside the locked office of the principal investigator (PI) whenever not in use. Contact forms are stored separately from any survey data collected in this study (the survey data are collected via computer and immediately housed in a password-protected secure database). The names of participants are kept in encrypted files on a password-protected server behind the university computer system’s firewall.

For implementation data, quantitative data from feedback surveys and observations are initially entered into REDCap and a programmatic database, also located on the password-protected shared drive. They are then exported and imported into Dedoose, a qualitative data analysis software (2025), where qualitative and quantitative indicators can be integrated by study site for the purposes of analysis.

### Analytic Methods

#### Statistical Analyses

Descriptive statistics will be used to summarize the sample with regard to baseline characteristics of interest. Means and SDs will be presented for continuous variables, while sample proportions will be provided for categorical variables. Ninety-five percent CIs will accompany all sample statistics.

#### Analytic Approach

Analyses are tailored to the quasi-experimental design (with considerations for clustered data by neighborhood) and aligned with the study aims. The primary independent variable of interest is treatment assignment at the neighborhood level (intervention vs comparison). Dependent variables include both individual-level outcomes (eg, collective efficacy and exposure to community violence) and neighborhood-level outcomes (eg, collective efficacy aggregated to the neighborhood, police-reported crime, and violence rates). Models will incorporate both fixed effects (eg, treatment, baseline values, and covariates) and random intercepts to account for clustering where appropriate. Inferences will rely on cluster-robust SEs with small-sample corrections (df=6). Effect sizes and 95% CIs will be reported throughout, with emphasis on estimation and interpretation of magnitude rather than binary hypothesis testing.

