### Sample Size and Power

For the primary outcome in aim 1, individual-level neighborhood collective efficacy, the necessary sample size was calculated based on traditional methods that assume a fixed number of clusters. Using a 2-sided alpha of .05 and small-sample cluster-robust adjustments with 6 degrees of freedom, the study achieves 80% power to detect meaningful effects at the individual level. Specifically, the trial can detect a standardized mean difference of about 0.66 when the intraclass correlation coefficient (ICC) is 0.05. Under more conservative assumptions, the detectable effect size is approximately 0.83 when the ICC is 0.10 and 1.10 when the ICC is 0.20. These values highlight that the study is positioned to identify moderate to large individual-level intervention effects. By quantifying these detectable ranges, the trial not only clarifies its current analytic capacity but also establishes concrete guidance for future community trials, where additional neighborhoods or larger enrollments could be used to target smaller effects of substantive interest.

For aim 2, which evaluates neighborhood-level outcomes such as collective efficacy and community violence, the unit of comparison is the neighborhood. The study includes 8 neighborhoods: 4 assigned to the intervention and 4 to the comparison. With 8 clusters, the design is best suited to identifying larger neighborhood-level effects, which ensures that any observed changes will be both meaningful at the community scale and informative for the field. Using a 2-sided alpha of .05 and small-sample cluster-robust adjustments with 6 degrees of freedom, the minimum detectable effect size was estimated. Without adjustment for baseline, the detectable standardized effect is approximately 1.8. As aim 2 analyses will adjust for baseline neighborhood measures, precision improves as the correlation between baseline and follow-up increases. For plausible baseline–follow-up correlations, the detectable effect sizes range from approximately 1.9 when the correlation is 0.60, to 1.7 when the correlation is 0.70, to 1.4 when the correlation is 0.80, and to 1.2 when the correlation is 0.85. Reporting these estimates provides a transparent picture of what can be inferred from this trial and creates clear parameters for planning future evaluations, where additional neighborhoods would allow the detection of smaller, yet still important, community-level changes.

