#### Aim 1 (Individual-Level Outcomes)

The individual is the unit of analysis, but clustering within neighborhoods is explicitly modeled. The independent variable of interest is neighborhood-level treatment assignment, with covariates including baseline individual scores, demographic characteristics (eg, age, sex, race or ethnicity, and education), and relevant neighborhood-level indicators. Continuous dependent variables will be analyzed using linear mixed effects models of the form:

Yij=β0+β1(treatmentj)+β2(baselineYij)+β3Xij+uj+εij,

where YijY_{ij}Yij is the outcome for individual iii in neighborhood jjj, XijX_{ij}Xij are individual covariates, uju_juj is a random intercept for neighborhood, and εij\varepsilon_{ij}εij is the individual-level error term. The random intercept uju_juj captures unobserved contextual influences shared by individuals in the same neighborhood (eg, social environment, policing, or community resources). By including uju_juj, the model allows each neighborhood to have its own baseline level of the outcome, and treatment effects are estimated net of this shared clustering. For binary dependent variables (eg, presence or absence of exposure to violence), generalized linear mixed models with a logit link will be used, also including a neighborhood random intercept.

The intercept term represents the expected outcome value when predictors are set to 0 (or to reference categories). In the context of these analyses, a random intercept for neighborhood allows the model to adjust for systematic differences between neighborhoods not explained by observed covariates. This ensures that individuals are not treated as statistically independent when they belong to the same neighborhood and that SEs correctly reflect the clustered design. Fixed intercepts anchor the regression line, providing the baseline level against which covariate and treatment effects are interpreted.

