#### Aim 2 (Neighborhood-Level Outcomes)

The neighborhood is the unit of analysis. The dependent variables are neighborhood-aggregated outcomes (eg, mean collective efficacy scores and rates of crime or violence). The independent variable is treatment assignment. The primary analysis will use an analysis of covariance specification, where the neighborhood-level outcome at follow-up is regressed on treatment assignment and the baseline value of the same outcome. This model provides an adjusted mean difference in follow-up outcomes between intervention and comparison neighborhoods, controlling for baseline heterogeneity. As only 8 clusters are available, models will not include random effects but will instead rely on cluster-robust variance estimators with small-sample corrections. Adjustment for additional neighborhood-level covariates (eg, baseline socioeconomic disadvantage, racial composition, and baseline crime levels) will be included cautiously in sensitivity analyses, given the limited degrees of freedom. These covariates will be added one at a time to assess the robustness of the primary results. Sensitivity analyses will also include difference-in-differences models, where the dependent variable is the change from baseline to follow-up. Results will be expressed as standardized effect sizes for comparability across outcomes and to provide planning parameters for future trials.

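### A single df=6 does not fit models that adjust for a neighborhood-level value: the Aim 2 primary ANCOVA has 5 df, and 4 with one added covariate

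*Protocol article*

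**What the plan says.** Analytic Approach gives one inferential rule for both aims: "Inferences will rely on cluster-robust SEs with small-sample corrections (df=6". Sample Size and Power uses the same count for the neighborhood-level aim: "Using a 2-sided alpha of .05 and small-sample cluster-robust adjustments with 6 degrees of freedom, the minimum detectable effect size was estimated". It describes the design as follows: "The study includes 8 neighborhoods: 4 assigned to the intervention and 4 to the comparison".

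Under Aim 2 (Neighborhood-Level Outcomes), the neighborhood is the unit of analysis. In the primary model, "the neighborhood-level outcome at follow-up is regressed on treatment assignment and the baseline value of the same outcome". On variance estimation, "models will not include random effects but will instead rely on cluster-robust variance estimators with small-sample corrections". Sensitivity analyses add further neighborhood covariates singly, and a difference-in-differences model takes the change score as outcome. The section acknowledges that degrees of freedom are scarce but gives no number below 6.

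Under Aim 1 (Individual-Level Outcomes), the covariates named in the text, besides the individual baseline score, are "demographic characteristics (eg, age, sex, race or ethnicity, and education), and relevant neighborhood-level indicators". The displayed equation contains treatment, the individual baseline, individual covariates and a neighborhood random intercept. It has no neighborhood-level covariate.

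The type of small-sample correction is not named anywhere.

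**The concern.** Treatment varies only between neighborhoods, so its precision is judged against eight units. Two arm means leave 6 df. Every neighborhood-level regressor beyond treatment costs one more, and the Aim 2 primary model has one by construction. A t(6) reference distribution is then too tight for that model, and tighter still relative to the truth in the models meant to show robustness.

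The robust variance does not remove the problem by itself. With one value per neighborhood, a cluster-robust variance is a heteroskedasticity-consistent variance on eight points: CR1, CR2 and CR3 become HC1, HC2 and HC3. These behave very differently at that size.

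What is at stake is the coverage of the 95% CIs that the article promises throughout, and the detectable effects that it offers as planning parameters for later trials.

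**Working it through.** **Inputs.** From Sample Size and Power: 8 neighborhoods, 4 versus 4; two-sided alpha 0.05; 6 df; baseline–follow-up correlations r of 0.60, 0.70, 0.80 and 0.85. Power of 80% is stated for Aim 1 ("the study achieves 80% power to detect meaningful effects at the individual level"). It is assumed for Aim 2, where it reproduces the adjusted figures.

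**1. Count the parameters (Aim 2, 8 rows).**
- Primary ANCOVA: intercept, treatment, baseline = 3, so 8 − 3 = 5 df.
- One added neighborhood covariate: 4 parameters, so 4 df.
- Change score on treatment only: 2 parameters, so 6 df. The stated value is right here.

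**2. Reproduce the article's adjusted detectable effects.** MDE = (t[.975, df] + t[.80, df]) × sqrt(2/4) × sqrt(1 − r²). The bracket is 3.353 for 6 df, 3.490 for 5 df and 3.717 for 4 df. At r = 0.60 with 6 df: 3.353 × 0.7071 × 0.8 = 1.90.

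| r | Stated | 6 df | 5 df | 4 df |
|---|---|---|---|---|
| 0.60 | 1.9 | 1.90 | 1.97 | 2.10 |
| 0.70 | 1.7 | 1.69 | 1.76 | 1.88 |
| 0.80 | 1.4 | 1.42 | 1.48 | 1.58 |
| 0.85 | 1.2 | 1.25 (1.249) | 1.30 | 1.39 |

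All four stated values match 6 df after rounding, and none matches 5 df. So 6 df was applied to the baseline-adjusted model. (The unadjusted figure of 1.8 does not reproduce: the same formula gives 2.37. That is a separate matter and this point does not rest on it.)

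**3. Effect of the wrong reference distribution, for any given standard error.** Critical values t(.975) are 2.447 (6 df), 2.571 (5 df) and 2.776 (4 df).
- CI width relative to the right one: 2.447/2.571 = 0.952, so 4.8% too narrow; 2.447/2.776 = 0.881, so 11.9% too narrow.
- With model-based standard errors, P(|t(5)| > 2.447) = 0.058 and P(|t(4)| > 2.447) = 0.071.
- An observed t of 2.5 has p = 0.047 on 6 df, 0.054 on 5 df and 0.067 on 4 df.

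**4. Add the behavior of the robust standard errors.** Null simulation with 8 points, 4 versus 4, r = 0.7, equal error variance, and a baseline difference between arms of 0 or 1 SD. Type I error at nominal 5%:

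| Standard error and cutoff | ANCOVA (0 / 1 SD) | One added covariate (0 / 1 SD) |
|---|---|---|
| CR1, t(6) | 6.9% / 8.3% | 9.4% / 10.5% |
| CR2, t(6) | 6.6% / 7.9% | 8.8% / 9.4% |
| CR3, t(6) | 3.1% / 3.6% | 2.8% / 3.2% |

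Model-based standard errors with t on residual df gave 4.8% to 5.1% throughout. The change-score model with CR1 or CR2 and t(6) gave 5.0%.

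The Satterthwaite df for CR2 has a median of about 4.1 in the ANCOVA, 3.2 with the 1 SD baseline difference, and 2.9 with the added covariate.

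**5. Aim 1.** A null simulation of the random-intercept model, with an assumed and known ICC of 0.10 and a t(6) cutoff, gave 5.9% for CR2 when the individual baseline was the only covariate. With one neighborhood-level covariate it gave 7.0% (CR2), 10.9% (CR1) and 3.3% (CR3).

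**The case against.** **The direction is not settled by the text.** A reader might infer that p-values are too small and intervals too narrow in every model that adjusts for a neighborhood value. The article does not support that. It promises a small-sample correction without naming it, and CR3 or the jackknife is a standard one. Combined with t(6) it over-covers, rejecting about 3% of the time. This stands. It does not rescue 6 as the df, but it makes the net error conditional on the correction.

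**Aim 1 may not be affected.** The displayed model has individual covariates only, and there t(6) is approximately right. Neighborhood-level indicators are mentioned once, without a list or number. A reader might take a much larger error rate, obtainable by assuming several such covariates and a crude correction, as the error rate of the primary analysis. Nothing in the article fixes those assumptions, so no such rate should be attributed to this study.

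**The consequences are limited.** The primary outcome is individual-level collective efficacy, and the neighborhood outcomes are secondary. The larger inflation is confined to sensitivity models that the article already treats with caution, and reporting is to emphasize magnitude over testing. This bears on severity. It does not bear on coverage, because intervals are the stated product.

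**Robust standard errors are defensible.** In Table 1 every comparison area (2,777 to 5,534 residents) is smaller than every intervention area (7,517 to 12,981). If error variance scaled as 1/population, which is an assumption, model-based standard errors on residual df would reject 5.4% to 5.8%. So moving to model-based standard errors is a choice, not a necessity.

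The degrees of freedom cannot be put down to detail left to a fuller plan. The article states a number, and its own detectable effects show that the number was used in the adjusted model.

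**Conclusion.** The blanket 6 df is wrong as written for models that adjust for a neighborhood-level value. The Aim 2 primary ANCOVA has 5, and each model with one added covariate has 4. The count itself needs no assumption beyond one row per neighborhood, which the Aim 2 section implies.

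The df error alone is modest in the primary Aim 2 model and roughly doubles with one added covariate. The simulated rates for CR1 and CR2 rest further on r = 0.7, equal error variance and a baseline difference of at most 1 SD. Under CR3 the result would be conservative, so under-coverage is a likely consequence and not a certain one.

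The adjusted detectable effects are understated by about 4% (3.490/3.353 = 1.041), given 80% power and a baseline uncorrelated with treatment.

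The 6 df is correct for the change-score model and approximately correct for Aim 1 with individual-level covariates only.

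**What to change.** Replace the single df=6 with degrees of freedom set per model, by one of two routes:

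- **Model-based standard errors with t on 8 − p df:** 5 for the ANCOVA, 4 with one added covariate, 6 for the change score.
- **CR2 standard errors, named as such, with Satterthwaite df computed for each model.** Median df of about 3 to 4 imply critical values roughly 12% to 33% larger than t(6). In the same simulations this route was slightly conservative (3.6% to 3.9%).

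CR2 with simple residual df is not enough: it still rejected 5.8% to 6.9% in the ANCOVA.

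For Aim 1, keep neighborhood-level indicators out of the primary model. Otherwise subtract one df for each, or use Satterthwaite df.

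Under Sample Size and Power, restate the baseline-adjusted detectable effects on 5 df: about 2.0, 1.8, 1.5 and 1.3 (1.97, 1.76, 1.48 and 1.30).

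The cost is a change of wording and wider intervals, mainly for the secondary neighborhood outcomes. On the first route they are about 5% wider in the ANCOVA (2.571/2.447) and 13% wider with one added covariate (2.776/2.447), relative to t(6). On the second they are wider still. The Results section says that analysis began in April 2026 and publication is expected in 2027, so the change should be recorded as a dated correction before results are reported.

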#### Aim 1 (Individual-Level Outcomes)

The individual is the unit of analysis, but clustering within neighborhoods is explicitly modeled. The independent variable of interest is neighborhood-level treatment assignment, with covariates including baseline individual scores, demographic characteristics (eg, age, sex, race or ethnicity, and education), and relevant neighborhood-level indicators. Continuous dependent variables will be analyzed using linear mixed effects models of the form:

Yij=β0+β1(treatmentj)+β2(baselineYij)+β3Xij+uj+εij,

where YijY_{ij}Yij is the outcome for individual iii in neighborhood jjj, XijX_{ij}Xij are individual covariates, uju_juj is a random intercept for neighborhood, and εij\varepsilon_{ij}εij is the individual-level error term. The random intercept uju_juj captures unobserved contextual influences shared by individuals in the same neighborhood (eg, social environment, policing, or community resources). By including uju_juj, the model allows each neighborhood to have its own baseline level of the outcome, and treatment effects are estimated net of this shared clustering. For binary dependent variables (eg, presence or absence of exposure to violence), generalized linear mixed models with a logit link will be used, also including a neighborhood random intercept.

The intercept term represents the expected outcome value when predictors are set to 0 (or to reference categories). In the context of these analyses, a random intercept for neighborhood allows the model to adjust for systematic differences between neighborhoods not explained by observed covariates. This ensures that individuals are not treated as statistically independent when they belong to the same neighborhood and that SEs correctly reflect the clustered design. Fixed intercepts anchor the regression line, providing the baseline level against which covariate and treatment effects are interpreted.

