#### Site Eligibility Criteria, Selection Process, and Study Setting

This study includes 8 neighborhood sites in the greater Pittsburgh, Pennsylvania, region. Four neighborhoods were initially chosen as intervention sites based on having high levels of gun and community violence incidents and desiring or engaged in efforts to increase community safety and identified as priority neighborhoods by the Allegheny County Department of Human Services, Office of Behavioral Health, interested community partners, and the project Steering Committee. The Steering Committee guides and informs the project and includes community partners, resident facilitators, interdisciplinary and countywide partners, and research team members.

To identify 4 comparison sites, the team used a process we refer to as, “participatory propensity score matching.” Building on the work of the abovementioned stakeholder groups, the research team constructed a list of 29 additional neighborhoods that were similarly high in violence. Steering Committee members then rated the identified neighborhoods in terms of appropriateness and need, recommending the removal of 5 neighborhoods that were least comparable. The research team then calculated propensity scores for the remaining 24 neighborhoods.

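### Aim 1 credits the random intercept with adjusting for unexplained neighborhood differences; with non-randomised neighborhood-level treatment it handles only correlation, so any residual arm difference stays in the treatment coefficient, in either direction

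*Protocol article*

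**What the plan says.** The protocol article, Aim 1 (Individual-Level Outcomes), gives the model as "Yij=β0+β1(treatmentj)+β2(baselineYij)+β3Xij+uj+εij". It adds: "The independent variable of interest is neighborhood-level treatment assignment, with covariates including baseline individual scores". Demographic characteristics and relevant neighborhood-level indicators are also listed as covariates.

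The section describes the random intercept as holding unmeasured shared context, with the social setting, policing and local resources as examples. It then makes two statements about what the intercept does:

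- "the model allows each neighborhood to have its own baseline level of the outcome, and treatment effects are estimated net of this shared clustering"
- "a random intercept for neighborhood allows the model to adjust for systematic differences between neighborhoods not explained by observed covariates"

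The sentence after the second statement gives a narrower role: people from one neighborhood are not treated as independent, and standard errors reflect the clustering.

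The Evaluation Design section says the design is quasi-experimental because the CRCEI was already running in the intervention sites. Under Site Eligibility Criteria, Selection Process, and Study Setting, those sites were chosen for high levels of violence and also for "desiring or engaged in efforts to increase community safety and identified as priority neighborhoods". Comparison sites were then matched on census-type variables, with steering committee review.

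For Aim 2 the article states: "Sensitivity analyses will also include difference-in-differences models, where the dependent variable is the change from baseline to follow-up". The Aim 1 section names no counterpart.

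**The concern.** A random intercept is a mean-zero term that the model takes to be independent of the other predictors, including treatment. It lets neighborhoods vary around a common level within each arm. It does not compare like with like across arms. When treatment is itself a neighborhood attribute, the average neighborhood effect in the intervention arm minus that in the comparison arm cannot be told apart from the treatment coefficient β1. The model yields an estimate only by assuming that this average difference is zero apart from chance.

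Randomisation would justify that assumption. Here it has to be argued from matching and covariates. The two statements suggest instead that the model has dealt with unexplained neighborhood differences. The Discussion adds that selection bias should be minimal because of the propensity matching. A reader of the primary result could then give β1 a causal reading that it cannot carry without the assumption being stated.

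**Working it through.** **Inputs from the article.** 8 neighborhoods, 4 per arm; 111 intervention and 151 comparison participants; two-sided alpha 0.05; 6 degrees of freedom; detectable differences 0.66 / 0.83 / 1.10 SD at ICC 0.05 / 0.10 / 0.20.

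**Plan's own figures, for scale.** With multiplier t(0.975, 6) + t(0.80, 6) = 3.353 and average cluster sizes 111/4 = 27.75 and 151/4 = 37.75:

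MDES = 3.353 × sqrt[(1 + 26.75·ICC)/111 + (1 + 36.75·ICC)/151]

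- ICC 0.05: 3.353 × sqrt(0.02106 + 0.01879) = 0.669
- ICC 0.10: 0.849
- ICC 0.20: 1.125

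These are within about 2.3% of the stated values. The point here is bias, so it leaves them unaffected.

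**Step 1: identification.** Eight neighborhood indicators plus the treatment column make 9 columns of rank 8. Treatment is an exact combination of neighborhood indicators. Only the assumption that the intercepts are independent of treatment separates the two.

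**Step 2: what each model leaves behind.** Suppose there is no treatment effect. Let d1 and d3 be the residual arm differences at T1 and T3 after matching and the other covariates, and β2 the baseline slope. Approximately:

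- baseline-adjusted model: E(β1) = d3 − β2·d1
- change-based model: E = d3 − d1

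With β2 = 0.6 (assumed):

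| Case | Baseline-adjusted | Change-based |
|---|---|---|
| Stable difference, d3 = d1 = d | 0.4·d | 0 |
| Difference shrinks to d3 = 0.6·d | 0 | −0.4·d |
| Difference arises after T1, d1 = 0, d3 = d | d | d |

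For the stable case the bias is 0.4 × 0.3 = 0.12 SD and 0.4 × 0.5 = 0.20 SD. With d = −0.3 it is −0.12 SD. In the shrinking case the change-based model has bias −0.12 and −0.20 SD at the same two values, and the planned model has none. In the third case both models carry the whole difference.

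**Step 3: simulation of the stable case.** Assumed: no true effect, ICC 0.05, T1–T3 correlation or baseline reliability 0.6, 4 + 4 neighborhoods, 262 people. Mean β1:

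| Analysis | d = 0.3 | d = 0.5 |
|---|---|---|
| Baseline-adjusted, t-test on neighborhood means (3,000 runs) | 0.12 | 0.19 |
| Mixed model (300 runs) | 0.11 | 0.19 |
| REML mixed model (250 runs) | 0.10 | 0.21 |
| OLS with baseline, no random intercept (300 runs) | 0.11 | 0.19 |
| Mixed model without the baseline score (300 runs) | 0.28 | 0.49 |

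OLS gives the same bias as the mixed model from the same set of runs, so the intercept removes none of it. The baseline score does the work. For a 0.3 SD difference arising after T1, the mixed model gave 0.31.

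**The case against.** The strongest reply is that this is loose wording and no more. The next sentence gives the correct role of the intercept, the other phrase speaks of clustering and not confounding, and nowhere does the article say in terms that differences between arms are removed. That is fair as far as it goes. But the following sentence adds a correct property without withdrawing the incorrect one, and the incorrect one concerns systematic, unexplained neighborhood differences in a model where treatment is a neighborhood attribute.

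Four stronger readings are tempting, and the documents do not support them.

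- *The model leaves the whole arm difference in place.* It does not. Matching, the baseline score, demographics and neighborhood-level indicators all reduce it, and only the remainder counts. There is reason to expect some remainder: collective efficacy is not among the listed matching variables. On population, which is listed, Table 1 shows no overlap (7,517–12,981 against 2,777–5,534). Neither fact gives its size on the outcome.
- *The bias favours the CRCEI.* Engagement in safety efforts might raise baseline collective efficacy in the intervention sites. High violence, also a selection criterion, is linked in the Introduction to low collective efficacy. The direction is open.
- *Difference-in-differences is the right model and the planned one is inferior.* The second row of the table in Step 2 shows the reverse when the arm difference regresses toward a common mean. An advantage for change scores follows from assuming stability.
- *Aim 1 has no such sensitivity analysis.* The article is condensed and a full analysis plan may contain one. What can be said is that the article names it for Aim 2 and not under Aim 1.

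The article also labels the study quasi-experimental throughout and stresses estimation over testing. The first is proper disclosure. The second makes bias in the estimate the relevant harm.

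**Conclusion.** The statement about the random intercept is wrong and should be corrected. The intercept accounts for within-neighborhood correlation. β1 is a treatment effect only if no unmeasured arm-level confounding remains, given the matching and covariates.

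The size in this study cannot be determined, because T1 collective efficacy by arm is not reported. Under the assumptions shown, a stable residual difference of 0.3 or 0.5 SD gives a bias of about 0.12 or 0.20 SD. That is about 18% or 30% of the stated detectable effect of 0.66 SD (0.12/0.66 and 0.20/0.66), with the sign of the difference. A lower baseline correlation would leave more. If the difference instead regresses in line with the baseline slope, the planned model has no bias. These figures illustrate the mechanism and do not estimate the trial's bias. The finding limits what the primary result can claim; it does not show that the planned model should be replaced.

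**What to change.** In the Aim 1 section:

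1. Reword both statements so that the random intercept accounts for within-neighborhood correlation and its effect on standard errors, and nothing more. State that β1 assumes no unmeasured arm-level confounding given the matching and covariates.
2. Report T1 collective efficacy by arm.
3. Add, unless the full analysis plan already has it, a change-based sensitivity analysis: T1, T2 and T3 scores as outcomes, fixed neighborhood intercepts, arm-by-time terms and neighborhood-clustered inference. The arm-by-time terms vary within neighborhoods, so they are estimable. Show the result beside the baseline-adjusted estimate.
4. Say that the baseline-adjusted model is unbiased if the arm difference regresses toward a common mean in line with the baseline slope, and the change-based model if the difference is stable. Neither assumption can be tested here, neither model corrects the other, and neither handles differing time trends.

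The cost is wording and one extra model on data already collected. The change-based estimate is somewhat less precise when the T1–T3 correlation is low, and the causal claim becomes more modest.
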